### Secondary and tertiary outcome analyses

Statistical analysis of the pre-specified secondary endpoints will be performed with descriptive and inductive statistical methods. Survival data will be described by Kaplan–Meier plots and survival distributions will be compared using the log-rank test. Ordinal scores and non-normally distributed metric measures will be analyzed using non-parametric methods, including calculation of the median and quartiles and comparison of distributions using the Mann–Whitney U test. In case of normally distributed metric measures parametric methods will be used, including calculation of the mean and standard deviation and comparison of distributions using Student’s t-test. Binary data will be presented by contingency tables and rates will be compared using the Chi-squared test. Secondary and tertiary outcome analyses are considered not to be confirmatory. The *p* values are regarded noticeable in case *p* ≤0.05. No adjustment for multiple testing will be performed. Therefore, an overall significance level is not determined and cannot be calculated.

Additional exploratory analyses will include model-based analyses, subgroup analyses and safety analyses. In safety analyses, all study patients will be included (safety population).

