### Outcomes

The primary endpoint is overall survival in a 90-day follow-up period. If the difference in overall survival is significant, the treatment effect will be estimated by means of the 90-day all-cause mortality rate in both treatment groups.

Secondary outcomes include:Overall survival in a 28-day and 60-day follow-up period;Overall survival in a 1-year follow-up period;Clinical evidence of organ dysfunction (daily SOFA scores while in the ICU);Recovery of renal function as defined in the KDIGO guidelines [6];Requirement of haemodialysis after day 28 and day 60;Duration of renal support;ICU and hospital length of stay; andMarkers of inflammation, oxidative stress, cellular hypoxia and coagulation.

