### Objectives and aims

#### Aim 1

To compare the clinical efficacy between early and late initiation of renal replacement therapy in critically ill patients with AKI, we are testing the following:Hypothesis I: early initiation of renal replacement therapy in the treatment of critically ill patients with AKI will reduce mortality at 90 days compared to late initiation.

#### Aim 2

To understand the mechanisms of illness and recovery and how the RRT implementation strategies affect them, we are testing the following:Hypothesis II: early and late RRT are associated with differences in the expression of markers of illness and recovery.

#### Aim 3

We aim to assess the costs and cost-effectiveness of both strategies.

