### Power and sample size

Power calculations are performed based on the primary endpoint, i.e. the overall survival in a 90-day follow-up period. The primary efficacy analysis is intended to test whether early versus late initiation of RRT in intensive care patients with AKI results in different overall survival in a 90-day follow-up period.

An adaptive design based on a group sequential plan according to O’Brien and Fleming with one interim analysis and a global (two-sided) significance level α = 0.05 is applied (see below). The expected 90-day mortality rate in the control group with late initiation of RRT is 55 % (based on literature research [7–10, 20–24]). Differences between treatment groups are to be detected with a power of 80 %, if the 90-day mortality rate in the experimental intervention group with early initiation of RRT is 37 % or smaller. The expected treatment effect of 18 % is calculated on the mortality differences between the early and late groups resulting from the studies of our literature research [7–10, 20–24] (see Additional file 3). The interim analysis is conducted at the time when half of the total number of deaths has been observed (information rate 0.5). Follow-up of each patient will be 90 days. Resulting from these considerations, the interim analysis is performed after 53 deaths have been observed across both treatment groups. The final analysis is planned to be performed after 106 deaths have been observed in total across both treatment groups, i.e. assuming an average of 46 % mortality rate in the 90-day follow-up period, a total number of 106/0.46 = 230 patients across both treatment groups is included in the final analysis. This corresponds to 256 recruited patients, if an expected number of 10 % of recruited patients is assumed to be lost to follow-up and in the worst case has completely non-evaluable data. Power calculations are to be performed based on a two-sided inverse normal log-rank test [25], using ADDPLAN software (ICON, Dublin, Ireland).

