### Interim analysis

A group sequential plan according to O’Brien and Fleming with one interim analysis is established. In order to maintain a global significance level alpha = 0.05, the interim and the final analysis are performed on local significance levels of 0.0052 and 0.0480, respectively. Based on the group sequential plan, an adaptive design is applied, that admits two possible design changes after the interim analysis: i) the number of deaths of the final analysis will be re-calculated applying the inverse normal method [26]; and ii) the schedule and the number of further interim analyses may be modified applying the conditional rejection error probability (CREP) principle [27, 28].

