**Fig. 3 Fig3:**
[figure not shown]
Statistical analysis with per-protocol principle. Patients with protocol violation will be excluded in the analysis to analyze the effect of both treatment arms. Protocol violation is defined as: subjects in the early group who did not receive RRT in the early phase of AKI (KDIGO stage 2); and subjects in the late group who did not receive RRT, although KDIGO stage 3 was achieved

In a first approach, the primary outcome is evaluated (overall survival in a 90-day follow-up period) using a two-sided inverse normal log-rank test [21]. The only difference to the primary analysis is that a per-protocol approach is pursued instead of an intention-to-treat analysis.In a second approach, data are reduced from the original primary outcome to the binary outcome ‘90-day mortality from all causes’. The binary outcome is created in order to provide comparability to other published study results. It is evaluated using a two-sided Chi-squared test.

Further statistical analyses of the primary outcome will be performed in order to address the fact that study patients have different risk profiles at the time of RRT initiation. The efficacy of the experimental and the control treatment may differ depending on the patient’s risk profile. For example ‘high risk’ patients may benefit from experimental treatment with early initiation of RRT substantially compared to control treatment, whereas in ‘low risk’ patients the ‘late’ approach may be superior. In order to address these questions, multivariable statistical analyses will be performed using Cox regression. Overall survival is modelled as a function of baseline risk (determined by pre-randomization baseline data such as the patient’s age, Acute Physiology and Chronic Health Evaluation (APACHE) score and SOFA score, as well as the baseline medical condition, i.e. severe sepsis/use of catecholamines/refractory fluid overload/development or progression of non-renal organ dysfunction), RRT treatment and the interaction of baseline risk and RRT treatment. In three different model approaches, RRT treatment is expressed in terms of: i) a time-dependent covariate that impacts survival starting with the time of RRT initiation; ii) the randomized treatment group; and iii) the time to initiation of RRT.

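### SOFA is compared between arms with an unadjusted test although a pre-randomisation SOFA score is collected: valid, but an avoidable loss of precision (minor)

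*Protocol article*

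**What the plan says.** All references are to the protocol article.

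- **Outcomes** lists as a secondary endpoint "Clinical evidence of organ dysfunction (daily SOFA scores while in the ICU"), and separately a panel of coagulation, hypoxia, oxidative-stress and inflammation markers.
- **Secondary and tertiary outcome analyses** assigns a test by type of scale: "Ordinal scores and non-normally distributed metric measures will be analyzed using non-parametric methods, including calculation of the median and quartiles and comparison of distributions" with the Mann–Whitney U test, and "In case of normally distributed metric measures parametric methods will be used", with Student's t-test. No baseline value or stratification factor enters either test. The section calls these analyses non-confirmatory, treats p ≤ 0.05 as noticeable, and announces further exploratory model-based analyses without naming an endpoint or covariate.
- **Primary outcome analyses** counts the "Acute Physiology and Chronic Health Evaluation (APACHE) score and SOFA score" among the data available before randomisation. It uses them as baseline risk in Cox models of overall survival.
- **Enrolment** stratifies randomisation by the cardiovascular SOFA item (0–2 versus 3–4) and by oliguria, and sets the day of randomisation as day 0.

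**The concern.** Critically ill patients differ widely in organ dysfunction at entry. When follow-up SOFA is compared without reference to the starting score, that spread stays in the error term. The article recognises that patients enter with different risk and models this for survival, but not where the outcome is SOFA itself.

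At stake is the precision of one pre-specified secondary endpoint. The trial is sized on deaths alone, so nothing else in the plan protects precision for SOFA. Its p-values will still be read, because the article sets a threshold for calling them noticeable. A real difference in organ dysfunction could be missed that the same data, analysed with the baseline score, would show.

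**Working it through.** **1. The plan's own figures.** The article states no power or precision for SOFA. Its sample size concerns deaths, and it reproduces:

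- The design is one where "a global (two-sided) significance level α = 0.05 is applied". Under proportional hazards, HR = ln(0.63)/ln(0.45) = 0.579.
- A two-look O'Brien–Fleming design at information 0.5 needs 105.7, so 106 deaths. Its local levels match the text, in which "the interim and the final analysis are performed on local significance levels of 0.0052 and 0.0480, respectively".
- 106/0.46 = 230 evaluable patients, and 230/0.90 = 255.6, so 256 recruited.

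None of this is affected by the present point. With 1:1 allocation it gives 115 evaluable patients per arm, used below.

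**2. Assumption.** The documents give no correlation (rho) between baseline and follow-up SOFA. I take 0.3 to 0.7.

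**3. Gain from adjustment.** ANCOVA multiplies the variance of the arm difference by 1 − rho². A two-sided 5% test with 80% power has a standardised effect of 2.8016, so adjusted power = Φ(2.8016/√(1 − rho²) − 1.96). The unadjusted detectable difference is 2.8016 × √(2/115) = 0.369 SD, and the adjusted one is that times √(1 − rho²).

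| rho | Variance ratio 1 − rho² | Power (80% unadjusted) | Detectable difference at 115 per arm |
|---|---|---|---|
| 0.3 | 0.91 | 83.6% | 0.352 SD |
| 0.5 | 0.75 | 89.9% | 0.320 SD |
| 0.7 | 0.51 | 97.5% | 0.264 SD |

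**4. Check on an ordinal scale.** Rounded SOFA-like scores were simulated (115 per arm, shift 0.37 SD, 4,000 trials per setting). Power of Mann–Whitney against rank ANCOVA was 77% vs 80% at rho 0.3, 78% vs 88% at 0.5 and 78% vs 96% at 0.7. The gain is therefore not an artefact of the normal formula, and at rho 0.3 it is only about 3 points.

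**5. If the tests were run on change from baseline.** With equal variances, a change score has variance 2(1 − rho) relative to the raw value:

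| rho | Raw | Change | ANCOVA |
|---|---|---|---|
| 0.3 | 1.00 | 1.40 | 0.91 |
| 0.5 | 1.00 | 1.00 | 0.75 |
| 0.7 | 1.00 | 0.60 | 0.51 |

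ANCOVA has the smallest variance in every row.

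**6. Chance imbalance.** With 115 per arm and no control of baseline, the chance baseline difference has a standard deviation of √(2/115) = 0.13 SD. Only rho times it reaches the follow-up difference, with 95% limits of ±1.96 × rho × 0.132. That is ±0.08, ±0.13 and ±0.18 SD at rho 0.3, 0.5 and 0.7. The standard error of the unadjusted test already includes this.

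**7. Limit on these figures.** Detectable differences in step 3 assume that all 230 patients have a SOFA value. SOFA is recorded only in the ICU, and the article expects 46% mortality by day 90. Later days will have fewer and more selected patients, and the baseline score may predict less. The figures are upper ones.

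**The case against.** **The analysis is valid and not confirmatory.** This stands. Randomisation protects the unadjusted test, no stated figure is wrong, and the primary endpoint is untouched. It limits the weight of the point but does not remove it.

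**The article does not say the raw value is tested; it could be change from baseline, and covariates may be in an analysis plan not shown.** The article is indeed silent on the variable tested. But it does name the tests, and they take no covariate. Step 5 shows that a change score is less precise than adjustment throughout the assumed range, and at rho 0.3 worse than the raw value. The announced exploratory models are additional and do not replace the named tests.

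**Adjustment does not solve the larger difficulty with SOFA, which is unobserved after death or ICU discharge.** This stands. It is a separate matter and no reason to leave out the baseline score.

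**A reader might infer that Aim 2, the hypothesis that "early and late RRT are associated with differences in the expression of markers of illness and recovery", loses precision as a whole.** The documents do not support this. Plasma NGAL is measured before entry as an inclusion criterion, but nothing shows that the outcome marker panel is sampled before randomisation. The workflow figure's legend places laboratory tests before RRT begins, and in the late arm that can be after randomisation.

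**A reader might also infer that chance imbalance passes in full into the arm difference and produces false findings.** Step 6 shows that only the fraction rho passes. It adds variance, not bias, and the error rate stays nominal.

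**Conclusion.** The point holds for SOFA, as a minor one. The article specifies between-arm tests without a covariate for an endpoint whose baseline value is collected, and so gives up precision that costs almost nothing to recover.

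Under an assumed correlation of 0.3 to 0.7, 80% power becomes about 84% to 97.5%, as upper figures. The 80% starting point is a reference level, since the article sets no target for SOFA. At the lower end of the range the gain is small. The point extends to a marker only if a pre-randomisation value of that marker exists.

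**What to change.** In Secondary and tertiary outcome analyses, make the between-arm comparison of SOFA baseline-adjusted: rank ANCOVA or a proportional-odds model with randomised arm, day 0 pre-randomisation SOFA and the two stratification factors (cardiovascular SOFA category and oliguria). Keep the raw medians and quartiles as description.

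Apply the same to a marker only where a pre-randomisation value exists. Do not use the sample taken before the start of RRT as the baseline, because in the late arm it can be post-randomisation and so affected by allocation.

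The cost is a change of wording and slightly more analysis. For SOFA the baseline is already collected, so no patients, visits or assays are added. A simple rule for missing baselines is needed, such as mean imputation. How to treat SOFA after death or ICU discharge still has to be settled separately.

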### Trial management

#### Protocol adherence

Initiation and close-out visits will be performed. The trial site will be regularly visited during recruitment and follow-up. The scope of these visits is to check compliance of the trial site with the study protocol and ‘good clinical practice’ rules. For all patients, the informed consent documents will be checked. In addition, source data verification of the key data (eligibility criteria, intervention, outcome measures) will be performed routinely in a random sample of 50 % of the patients. Monitoring will follow the standard operating procedure (SOP) based on the Technologie- und Methodenplattform für die vernetzte medizinische Forschung e.V. (TMF)-SOPs.

### Data collection and management

All trial-related processes will follow the SOPs. According to the SOPs, key documents and processes are subject to internal review. The data will be collected on paper CRFs and stored at the Department of Anesthesiology, Intensive Care and Pain Medicine at the University of Münster. Monitoring will include a timely query management process based on consistency and plausibility checks, combined with a dunning process for missing documentation.

### Safety

The Executive Committee is the management and decision-making body for the operational aspects of the study and will monitor the performance of the medical center and the quality of data collected. The Executive Committee will formulate publication plans and will oversee the publication and presentation of all data from the study. The Committee must grant permission before any study data may be used for presentation or publication.

## Discussion

The decision to start RRT in critically ill patients with severe AKI can depend on numerous factors and is, therefore, a complex process [8]. Timing of RRT has been difficult to study and has shown considerable variation between clinicians and institutions [29]. As a consequence, the question of the optimal timing of the initiation of RRT has not been solved yet [8–11, 13, 14]. Theoretically, initiation of RRT before the onset of severe AKI might influence patient outcomes. Specifically, early RRT might attenuate kidney-specific and non-kidney organ injury from acidemia, uremia, fluid overload and systemic inflammation, and potentially translate into improved survival and earlier recovery of kidney function [17, 18]. The results of three meta-analyses already showed that the early initiation of RRT might have a potential survival benefit for critically ill patients with AKI [12–14]. However, on the contrary, early initiation of RRT might involve patients who would recover renal function with conservative treatment alone. Consequently, this would result in unnecessary RRT with potential risks associated with RRT, raising an important ethical issue.

The ELAIN trial is a prospective randomized trial with the objective to analyze the influence of RRT timing on survival of critically ill patients with AKI. There are some aspects of the trial protocol that bear specific mention.

The study design contains a specific protocol that tends to minimize unnecessary RRT trying to prevent patients from avoidable RRT-related risks and improve patients’ outcome. In 2012, the KDIGO group published the KDIGO criteria for diagnosing AKI [6]. It has been shown that only 20 % of patients who develop KDIGO stage 2 progress to KDIGO stage 3 [30]. Sepsis and other severe conditions (e.g. hemodynamic instability manifested by hypotension requiring vasopressor support, refractory fluid overload) have been shown to be important risk factors for developing dialysis-dependent AKI [31, 32]. Therefore, the inclusion criteria chosen for the ELAIN trial were selected to identify patients who are at high risk for the need of RRT. In addition, we chose a biomarker-based model for the detection of patients with worsening AKI, because previous studies demonstrated that biomarkers can be used for identifying potential aggravation [16]. By using this patient-enrichment strategy, we excluded patients whom subsequently recovered from AKI spontaneously without requiring RRT. Plasma NGAL is one of the most studied biomarkers in the field of AKI. The diagnostic value for the detection of AKI might be controversial [33, 34] but for the need of RRT in critically ill patients it has been demonstrated as a good predictor [35, 36]. Thus, to reduce the risk of unnecessary RRT, we only include patients with KDIGO stage 2, concomitant disorders and elevated NGAL values [35].

Nevertheless, the ELAIN trial has some limitations. The power calculation is based on data published a long time ago. Although the mortality of dialysis-dependent AKI decreased over the last 20 years [37], the mortality is still unacceptably high. A recently published meta-analysis regarding the initiation of renal replacement therapy analyzed 15 trials published between 1985 and 2011 and the authors showed that the overall 28-day mortality across the 15 trials was 55 % [13]. Although this study included older studies, a recently published trial investigating critically ill patients with a dialysis-dependent AKI also demonstrated that the 60-day all-cause mortality in critically ill patients with a dialysis-dependent AKI is 52 % [38]. Another limitation of the study is that we include critically ill patients with AKI stratified by hemodynamic SOFA score and urinary output accepting heterogeneity due to the inclusion of septic and non-septic patients. The pathophysiology of septic AKI is unique resulting in differences in clinical outcomes and responses to renal replacement therapy compared to non-septic patients [31]. But implementing a specific protocol with homogenous criteria for the diagnosis of critical illness and acute kidney injury combined with biomarkers is the first step to filling an important knowledge gap. Another limitation of such a trial design is that the investigators cannot be blinded and consequently there is a risk of contamination or unequal prescription of co-interventions. However, we adequately take this into account by a clear monitoring of all interventions.

Several studies investigating the timing of continuous RRT in critically ill patients used the time from randomization to commencement of continuous RRT to define ‘early’ and ‘late’ [8, 39]. In our trial we use the severity of AKI based on the KDIGO criteria to define ‘early’ and ‘late’ initiation of continuous RRT. The initiation of RRT represents an escalation in the level of care and is associated with certain risks. In the past, it has been shown that the Acute Kidney Injury Network (AKIN) criteria alone cannot predict the progression of the severity of AKI [30]. But the biomarker NGAL has been shown to predict the progression of the severity of AKI [40, 41] and the need for RRT in critically ill patients [15, 35]. Therefore, we combine the KDIGO criteria with clinical risk factors and NGAL to increase the probability that we only include patients with severe AKI who subsequently need RRT and exclude patients who spontaneously recover from AKI. This might not be a validated approach, but the study results will show whether the combination of these factors can identify patients who subsequently develop a dialysis-dependent AKI.

The ELAIN trial is the first randomized controlled trial that includes a biomarker in a specific protocol plan to detect patients who will develop a severe, dialysis-dependent AKI. The results might be a significant contribution to the therapy of critically ill patients with acute kidney injury.

### Trial status

Recruitment is active.

## Abbreviations

AKI: acute kidney injury
AKIN: Acute Kidney Injury Network
APACHE: Acute Physiology and Chronic Health Evaluation
BUN: blood urea nitrogen
CREP: conditional rejection error probability
CRF: case report form
ECG: electrocardiogram
ELAIN: early versus late initiation of renal replacement therapy in critically ill patients with acute kidney injury
GFR: glomerular filtration rate
ICU: intensive care unit
KDIGO: Kidney Disease: Improving Global Outcomes
NGAL: neutrophil gelatinase-associated lipocalin
RRT: renal replacement therapy
SOFA: Sequential Organ Failure Assessment
SOP: standard operating procedure.
